CONNECT is a multi-component intervention that helps staff: learn new strategies to improve day-to-day interactions; establish relationship networks for creative problem solving; and sustain newly acquired interaction behaviors through mentorship. Complexity science and empirical research suggest that interaction patterns determine information flow, knowledge transfer, and capacity to monitor behaviors in healthcare settings [16,18,30]. In a preliminary test of CONNECT, we found support for the hypothesis that the intervention would improve staff interactions and reduce falls [31]. We propose that CONNECT, when combined with a content focused falls QI program (FALLS), will result in better resident outcomes when compared to FALLS alone. We chose falls for this test of CONNECT because: falls rates are high in nursing homes [32,33]; accepted practice guidelines and fall prevention programs exist [34-37]; and there is ample evidence from efficacy trials that multi-factorial risk reduction interventions reduce fall rates [3-5,13,38].

The study aims are to:

1. Compare the impact of the CONNECT intervention plus a falls reduction QI intervention (CONNECT + FALLS) to the falls reduction QI intervention alone (FALLS) on fall-related process measures in nursing home residents.

2. Compare the impact of CONNECT + FALLS to FALLS alone on fall-rates in nursing home residents, and determine whether these are mediated by the change in fall-related process measures.

3. Compare the impact of CONNECT + FALLS to FALLS alone on complexity science measures as reported by nursing home staff and determine whether these mediate the impact on fall-related process measures and fall rates.

To complete these aims we will use a cluster randomized, controlled trial design with the facility-level change in fall and complexity science measures as the primary outcomes. Because the CONNECT and FALLS interventions both encourage facility-wide change in staff behavior, randomization will occur at the facility level and subjects (nursing home staff and residents) are clustered within homes.

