#### Fall rate

Consistent with the MDS, we define a fall as an unintentional change in position resulting in a resident coming to rest on the ground or lower level [4] regardless of cause [2]. Recurrent falls are defined as two or more falls within the six-month study period [4]. These measures have been successfully employed in previous studies [2-4]. Due to underreporting of falls [94], data will be collected from multiple sources as shown in Table 3. We will calculate fall rates and recurrent falls as defined in the Table 3. From our previous falls study and national data, we assume a baseline fall rate of 1.5 falls/bed/year, and an average bed occupancy rate of 90-bed days/home/month. We therefore project that there will be a total of 2,160 falls in the study nursing homes over the study period. Proportion of repeat fallers and proportion of injurious falls (defined as proportion of falls resulting in injury including skin tear, hematoma, fracture, laceration, need for imaging or urgent assessment) will be measured as secondary fall endpoints.

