##### H3A

Staff in facilities randomized to receive CONNECT + FALLS will report significantly greater improvement from baseline immediately and three months after the intervention than staff in facilities receiving FALLS alone on complexity science measures of: communication openness, accuracy and timeliness; participation in decision making; relational coordination; psychological safety; and safety culture.

For these outcomes, we will use PROC MIXED to estimate a mixed model to estimates the effect of the intervention on each outcome averaged over time.

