### Statistical power

We used algorithms developed to estimate power for longitudinal models based on the formulae of Jung and Ahn [96], a type I error rate of 0.05 (two-tailed), and a 15% rate of attrition for the staff samples. Hierarchical linear modeling with SAS PROC Glimmix was used to account for clustering in this study. This procedure is useful when there are multi-level, nested sources of variability such as patient and staff clustering within nursing homes. The Glimmix procedure analyzes both individual and group level trajectories of change over time, and can be used to estimate models where persons within clusters are changing over time. Maximum cluster size was limited by the pool of resident fallers and number of staff in each facility. The power analysis algorithms used to determine cluster size take clustering at the individual level into account. In the analyses, we will treat cluster as a fixed rather than as a random effect. This approach will more adequately control on potential confounders at the level of the nursing home. With cluster analyzed as a fixed effect, inter-cluster correlations are not needed to calculate power.

For aim one, we will have 80% power to detect a 15% difference in risk factor assessment and intervention scores, which is considered to be the minimally clinically significant improvement in falls care practice. For aim two, the resident sample will provide 80% power to detect a 23% difference in the fall rate due to intervention, and a 23% difference in the probability of a recurrent fall. Because this is a real world effectiveness study, this change in fall rate is slightly smaller than that seen in a randomized controlled trial of multifactorial risk factor reduction, but still clinically meaningful. For the continuous outcomes in aim three, we will have 80% power to detect standardized differences of 0.21, a magnitude considered small in the statistical literature [97]. As we have a single primary outcome and several additional outcomes that are exploratory, we will not adjust our significance tests for multiple tests.

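### The waiver of multiplicity adjustment rests on one unnamed primary outcome, while the Background declares several primary outcomes

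*Protocol article*

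**What the plan says.** All references are to the protocol article.

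- **Statistical power.** The error rate is "a type I error rate of 0.05 (two-tailed), and a 15% rate of attrition for the staff samples". The section ends with the waiver: "As we have a single primary outcome and several additional outcomes that are exploratory, we will not adjust our significance tests for multiple tests". The single outcome is not identified there or elsewhere.
- **Background, after the three aims.** The design is described "with the facility-level change in fall and complexity science measures as the primary outcomes".
- **Fall rate.** The proportions of repeat fallers and of injurious falls "will be measured as secondary fall endpoints". Fall rate itself is given no rank.
- **Hypotheses.** H1A and H1B concern two process counts, H2A the fall rate, and H2B the probability of recurrent falls. H3A covers seven staff scales, on which staff in the combined arm "will report significantly greater improvement from baseline immediately and three months after the intervention".
- **Power by aim.** Aim 1 has "80% power to detect a 15% difference in risk factor assessment and intervention scores". Aim 2 has "80% power to detect a 23% difference in the fall rate due to intervention, and a 23% difference in the probability of a recurrent fall". Aim 3 has 80% power for a standardized difference of 0.21.

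**The concern.** The decision not to adjust has one stated reason, that only one outcome is primary. The Background gives a different account, in which fall measures and complexity science measures are primary together. An analysis plan written from this protocol cannot follow both.

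The rest of the article does not settle the matter. No hypothesis is called exploratory where it is set out, and each aim has its own 80% power statement. Recurrent falls are a powered hypothesis in one place, a secondary endpoint in another, and exploratory by implication in a third.

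What is at stake is the definition of trial success. As written, a nominal p below 0.05 on the fall rate, a process count or any one staff scale could be presented as a positive primary result, and a sentence in the protocol could be cited in support. The reported 5% error rate would then not describe the chance of a false claim of success.

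**Working it through.** **Step 1. Can the text be reconciled?**

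| Place | Status given to outcomes |
|---|---|
| Background, after the aims | Fall measures and complexity science measures are primary (plural) |
| Statistical power | One primary, unnamed; the others exploratory |
| Fall rate | Repeat fallers and injurious falls secondary; fall rate unranked |
| H1A to H3B | No rank given |

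The Fall rate section hints that fall rate leads among the fall endpoints. It does not touch the complexity science measures. It also does not rank the Aim 1 process counts, although these stand under the same Fall measures heading. The hint therefore does not produce a single primary outcome.

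**Step 2. Count the tests.**

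- Aim 1: 2 (H1A, H1B).
- Aim 2: 2 (H2A, H2B).
- Aim 3: 7 (openness, accuracy, timeliness, decision making, relational coordination, psychological safety, safety culture). H3A names two time points, but the analysis beneath it estimates one effect per scale averaged over time, so each scale counts once.
- Total: 2 + 2 + 7 = 11. The mediation hypotheses H2C and H3B are left out.

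**Step 3. Familywise error without adjustment.** For k independent tests at 0.05 under the complete null, the error is 1 − 0.95^k. The plan's own figure is recovered only at k = 1: 1 − 0.95 = 0.05.

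| Reading | k | 1 − 0.95^k |
|---|---|---|
| One named primary | 1 | 0.050 |
| One fall and one complexity measure | 2 | 0.0975 |
| Fall rate plus seven staff scales | 8 | 0.337 |
| All between-arm outcomes | 11 | 0.431 |

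**Step 4. Effect of correlation.** The article gives no correlations between outcomes, so these values are assumptions. I took jointly normal test statistics with a common correlation r and integrated the probability that none exceeds ±1.96:

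| k | r = 0 | r = 0.5 | r = 0.8 |
|---|---|---|---|
| 2 | 0.098 | 0.091 | 0.078 |
| 8 | 0.337 | 0.250 | 0.158 |
| 11 | 0.431 | 0.304 | 0.180 |

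If the 11 tests are correlated only within each aim (groups of 2, 2 and 7) and the aims are independent, the error is 0.363 at r = 0.5 and 0.276 at r = 0.8.

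**Step 5. Price of keeping several primaries.** A test with 80% power at two-sided 0.05 has expected z = 1.960 + 0.842 = 2.802. At the Bonferroni level 0.05/k, with critical value c, its power is Φ(2.802 − c):

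| k | 0.05/k | c | Power |
|---|---|---|---|
| 2 | 0.025 | 2.241 | 71% |
| 8 | 0.00625 | 2.734 | 53% |
| 11 | 0.00455 | 2.838 | 49% |

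This takes the stated 80% as given. Bonferroni is the simple bound; Holm would do somewhat better when several effects are real.

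**The case against.** The strongest reply is that the Statistical power section is the dedicated statistical statement, whereas the Background sentence mainly explains why homes are randomized. On that view the plural is loose wording and the single-primary statement governs. That is a fair reading and may be what the sponsor meant. It does not close the point, because the governing statement still fails to name the outcome.

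Several further objections stand and limit the claim:

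- A reader might count the seven scales at two time points, giving 2 + 2 + 14 = 18 tests and 1 − 0.95^18 = 60%. The Aim 3 analysis averages each scale over time, so the documents do not support that count.
- A reader might call all 11 outcomes confirmatory. The article does not. It labels repeat fallers secondary and calls the additional outcomes exploratory as a group. Only H3A speaks of significance, and a power statement does not make an outcome primary. The 43% is therefore an outer value.
- The independence assumption overstates the error. H1A and H1B share charts, H2A and H2B share fall events, and the staff scales share respondents.
- A reader might conclude that fall rate is clearly the intended primary. The Fall rate section ranks only repeat fallers and injurious falls below it, and nothing places the Aim 1 counts second.

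**Conclusion.** The inconsistency is real and follows from the article's own text. It is not a detail left to an analysis plan, because the protocol itself fixes both the rule and the reason for it. What can be said is that two sections disagree and that the waiver lacks support while both stand. To say outright that the single-primary premise is false would go too far, since the text does not show which section is the slip.

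On the Background's wording the unadjusted familywise error runs from 9.75% to about 34%, depending on how many measures it is taken to cover. The ceiling is about 43% for all 11 outcomes. These figures assume independence and a complete null. At an assumed common correlation of 0.8 they become about 8%, 16% and 18%, still above 5%. The contradiction itself depends on none of these assumptions.

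**What to change.** Before outcome data are analysed, name one primary outcome, use the same wording in the Background and in Statistical power, and label every other outcome secondary or exploratory. Fall rate per occupied bed-day needs the least rewriting, given the ranking in the Fall rate section. The choice is the sponsor's and should be confirmed explicitly against the Aim 1 process counts. Alpha then stays at 0.05, the stated power basis is unchanged, and design, sample and data collection are unaffected. The edit is about two sentences; its cost is that the remaining outcomes lose confirmatory status. A correction within the seven staff scales would then be optional.

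If several primaries are intended, list them, specify a procedure such as Holm, and restate power at the adjusted level. That route is costlier: under Bonferroni, 80% falls to about 71% with two primaries and 53% with eight.

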### Missing data

Item-specific missing data on potential covariates will be handled with maximum-likelihood and multiple imputation techniques [98]. Missing values can be imputed with SAS PROC MI using the Markov chain Monte Carlo algorithm, which can be used with complex missing data patterns as well as for continuous, ordinal, and dichotomous measures [99]. We expect 15% attrition on our dependent variables across waves. Recent work by Chang et al. [100] shows how shared parameter models [101,102] can be used to address potential bias due to a failure to meet the missing at random assumption. These models will be operationalized where necessary.

### Timeline

We were funded (56NR003178) to conduct a pilot study of the CONNECT + FALLS intervention in two nursing homes and FALLS in two nursing homes [31]. We have now been funded (R01NR003178) to conduct this study in 16 additional nursing homes to allow for a full test of the intervention. We will begin nursing home recruitment in fall of 2011 and will stagger recruitment and interventions over four years (completed in 2015). Follow-up data collection and analyses will be completed in 2016.

## Discussion

By focusing on improving local interaction behaviors, we propose that CONNECT is an innovative way to target the learning environment and maximize nursing home staff's ability to adopt content learned in a falls QI program and integrate it into knowledge and action. Preliminary results from the study suggest that local interaction behaviors can be improved in ways that effectively enable the staff to adopt evidence-based current practice for falls prevention [19,31]. We are confident that the capacity exists in most nursing homes to develop and focus these behaviors using existing staff and resources using CONNECT to enhance staff members' abilities to adopt QI interventions in the FALLS program. Because CONNECT is a systems intervention, it can be applied in future projects to examine adoption of other evidence-based practices for a wide variety of clinical problems such as pressure ulcers, pain, and depression and may apply to other healthcare setting.
